### Safety

All adverse events (AEs) and adverse reactions (ARs) will be reported in a timely fashion. AEs and ARs, whether expected or not, will be collected and recorded during clinical assessments at weeks 3 and 6 and 3-monthly for 6 months (NCI-CTC v5.0). When serious adverse events (SAEs) occur, an SAE form will be completed within 24 hours. The chief investigator will determine whether SAEs were ‘related’ (resulting from the administration of the study treatment or procedure) or ‘unexpected’ (an event not listed in the study protocol as an anticipated occurrence) and report this to the research ethics committee. Any questions concerning AE reporting will be directed to the chief investigator in the first instance. The chief investigator will notify the sponsor of all SAEs that occur.

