## Methods and analysis

### Trial objectives

The primary objective is to determine the incidence of adverse and serious adverse device events (ADEs/SADEs) overall and by severity, graded by the National Cancer Institute—Common Toxicity Criteria (NCI-CTC v5.0). The co-primary objective is to determine the objective response rate (ORR) with [^166^Ho]Ho-RE, defined as the rate of best overall response (which includes complete responses and partial responses) in the treated liver volume as determined by RECIST 1.1 and mRECIST. In addition, the total hepatic response and overall response will be assessed according to RECIST 1.1 and mRECIST.

The secondary objectives are quality of life (QoL) as determined using the European Organisation for Research and Treatment of Cancer (EORTC) questionnaires QLQ-C30 and HCC18 at baseline and every 3 months. Exploratory endpoints include the assessment of radiomics in the prediction of treatment response determined by CT scans of the liver at baseline, 12 weeks post RE and at disease progression. Biodistribution and dosimetry received to tumour and normal liver will be reported. The results of this study will be combined with the identical iHEPAR study.

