### Study procedures

Patients will undergo baseline tumour imaging including chest, abdominal and pelvic CT scan and MRI scan of the liver at screening (table 1). Up to 4 weeks following consent, patients will undergo angiography of the hepatic artery to assess the presence of aberrant vessels arising from hepatic arteries. If present, protective coiling of any extrahepatic branch (eg, aberrant segment IV and right gastric artery) will be undertaken. In the same session, a scout dose of maximum 250 MBq ^166^Ho-labelled microspheres, QuiremScout (Terumo Europe), will be injected into the hepatic artery via the same catheter position chosen for the scheduled RE session in order to calculate the hepatopulmonary shunt fraction. In cases of selective treatments, less activity will be injected for the scout, proportionally to the volume treated. Tracer distribution will be evaluated using [^166^Ho]Ho SPECT imaging. Following completion of the angiogram and scout imaging, a decision will be made regarding the dose to be delivered. The individualised treatment plan will attempt to optimise doses to achieve at least a tumour dose of 150 Gy while keeping normal liver doses to 45–60 Gy or lower. QuiremSpheres (Terumo Europe) will be administered up to 2 weeks following these investigations.

**Table 1 T1:** Treatment schedule

Procedures	Screening		Treatment	follow-up			
	Screening	Scout		W3	W6	M3	M6
Informed consent	X						
Inclusion/exclusion criteria	X	X	X				
Demographics	X						
Physical exam and clinical performance status (ECOG)	X					X	X
EORTC QLQ C30+HCC18	X					X	X
CT scan^*^	X						
MRI scan^†^	X		X			X	X
Tumour assessments (mRECIST)	X					X	X
SPECT/CT		X	X^‡^				
Angiography		X	X				
Scout dose		X					
Therapeutic dose			X				
Blood tests	X	X	X	X^§^	X^§^	X^§^	X^§^
(S)AE’s+Con Med	X			X	X	X	X

* CT scan chest + pelvis

† MRI liver with hepatic biliary contrast

‡ 3-4 days after treatment

§ No coagulation blood tests required

ECOG, Eastern Cooperative Oncology Group; EORTC, European Organisation for Research and Treatment of Cancer; mRECIST, modified Response Evaluation Criteria in Solid Tumors; SPECT, single-photon emission computed tomography.

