Patients will be admitted the day of the procedure and discharged the same day. In patients with bilobar disease, the first treatment will be administered to the lobe with the greatest tumour burden. Treatment of the contralateral lobe will be scheduled for 4–6 weeks after the first treatment. Following administration of QuiremSpheres, patients will receive standard of care post-RE treatment to prevent radiation-induced hepatitis and gastric complications: reducing dose of dexamethasone 8 mg daily for 1 week, 6 mg daily for the following week, 4 mg daily the week after that and 2 mg daily for 1 final week, proton pump inhibitor 60 mg daily and ursodeoxycholic acid 250 mg every night. A post-therapy SPECT will be performed 3–4 days after QuiremSpheres administration.

Patients will be reviewed in week 3, week 6 and on a 3 monthly basis for 6 months or until disease progression, withdrawal from the trial or death (whichever comes first). Blood tests will be performed at each visit for safety. Tumour imaging will be repeated 3-monthly post-RE for 6 months. The same method for assessment at baseline must then be used at all subsequent time points. mRECIST criteria will be used to determine patient response to treatment and ORR. QoL questionnaires (EORTC QLQ-C30) and EORTC HCC18 will be completed at baseline, and 3-monthly post-RE until trial completion.

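### Adverse-event collection is not scheduled at the scout session, the treatment session or the day 3–4 SPECT, so non-serious events close to device exposure rest on recall at week 3

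*Protocol article*

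**What the plan says.** Trial objectives makes safety primary: "The primary objective is to determine the incidence of adverse and serious adverse device events (ADEs/SADEs) overall and by severity". The Statistical analysis section adds timing to the features by which ADEs will be summarised.

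The Safety section begins with a general duty, "All adverse events (AEs) and adverse reactions (ARs) will be reported in a timely fashion", and then fixes when events are gathered: they "will be collected and recorded during clinical assessments at weeks 3 and 6 and 3-monthly for 6 months". Serious events have their own route: "When serious adverse events (SAEs) occur, an SAE form will be completed within 24 hours". A related serious event is one "resulting from the administration of the study treatment or procedure", so the procedure counts as well as the microspheres.

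In Table 1 (Study procedures), the row for (S)AEs and concomitant medication is marked at Screening, W3, W6, M3 and M6. It is blank under Scout and Treatment. Blood tests and angiography are marked under both of those columns, and each has its own microsphere dose. The text also places a SPECT 3–4 days after therapy, with no adverse-event check attached.

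For timing, "QuiremSpheres (Terumo Europe) will be administered up to 2 weeks following these investigations", and follow-up is described as "Patients will be reviewed in week 3, week 6 and on a 3 monthly basis for 6 months". For bilobar disease, "Treatment of the contralateral lobe will be scheduled for 4–6 weeks after the first treatment". Table 1 has a single Treatment column and does not show a second session.

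**The concern.** The device exposures in this trial are the scout injection and the therapeutic injection or injections. Events from angiography, embolisation and the first days afterwards are those most directly attributable to the device or procedure. The schedule has patients on site for each session and again at day 3–4, yet it first asks about adverse events at W3.

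A non-serious event that is not recorded cannot be told apart from an event that did not happen, so the rule against imputing missing primary-endpoint data gives no protection. Mild and moderate events, which contribute to the severity breakdown, are the ones most likely to be forgotten or given a wrong onset date. Concomitant medication has the same blank cells, although Study procedures describes several drugs started after administration.

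The data are to be pooled with iHEPAR, and the Discussion expects the combined analysis to set radiation safety thresholds for later randomised trials. Incomplete or mis-dated event records would carry through to that use.

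Bilobar patients raise a second question. They are exposed twice, but no visit is tied to the second exposure, and the article does not say from which treatment the weeks and months are counted.

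**Working it through.** The plan gives no figure of its own to reproduce here. The check compares the text with Table 1 and then works out intervals.

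**Step 1: text against table.** The post-treatment collection times in the Safety section (weeks 3 and 6, then 3-monthly to 6 months) match the marked cells W3, W6, M3 and M6. Table 1 adds Screening. Because two places agree, the blank Scout and Treatment cells are unlikely to be damage to the table.

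**Step 2: delay from exposure to first scheduled collection.** Inputs: scout to treatment 0–2 weeks (Study procedures); treatment to first adverse-event visit 3 weeks (Safety, Table 1).

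- From therapy: 3 weeks.
- From scout: (0 to 2) + 3 = 3 to 5 weeks.

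The SPECT visit lies 3–4 days after therapy, well inside this interval, and is not used for collection.

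**Step 3: second-lobe treatment.** Inputs: second treatment at week 4 to 6 after the first (Study procedures); M3 taken as week 13 and M6 as week 26 (my assumption). If the clock runs from the first treatment, the time from second treatment to visit is the visit week minus the week of the second treatment:

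| Second treatment at | W3 | W6 | M3 | M6 |
|---|---|---|---|---|
| week 4 | −1 | 2 | 9 | 22 |
| week 5 | −2 | 1 | 8 | 21 |
| week 6 | −3 | 0 | 7 | 20 |

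(weeks after second treatment; negative means before it)

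On this reading W3 always precedes the second exposure, W6 falls 0–2 weeks after it, and M3 falls 7–9 weeks after it. If the second treatment is at week 6, the next visit after that day is 13 − 6 = 7 weeks away.

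If the clock restarts at the second treatment, the visits fall 3 and 6 weeks after it, as for a single treatment, and the gap disappears. Nothing in Study procedures, Safety or Table 1 chooses between these readings.

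**The case against.** The strongest reply is that the plan does not confine recording to visits. The Safety section opens with a duty covering all adverse events and reactions, not only serious ones. Serious events trigger a form within 24 hours, including those caused by the procedure. Nothing limits W3 to events that begin at W3, so staff can record what happened earlier. Blood tests are taken at Scout and at Treatment, so laboratory values at those sessions are available. A blank cell shows that no entry is scheduled; it does not show that an event seen that day would be ignored. The article is also condensed, and the full protocol may state continuous collection. Finally, this is a 15-patient, non-comparative pilot with descriptive safety reporting.

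Much of this stands. A reader might infer that the primary endpoint misses the events closest to exposure. The documents do not support that, for the reasons just given. A reader might also infer that every bilobar patient is unobserved from about week 2 to week 7 after the second treatment. That holds only if visits are counted from the first treatment, which is not stated. Even then, M3 can record events since W6 and the reporting duties continue; the interval of about 7 weeks between W6 and M3 (13 − 6) applies to every patient. Nor does the article say that bilobar patients have the largest irradiated volume, or how many of the 15 will be bilobar.

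What the reply does not remove is the schedule as written. The general duty names no collection point, and the sentence after it ties collection and recording to the listed visits. The possible contents of an unseen protocol do not change what the Safety section and Table 1 state here.

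**Conclusion.** The point holds as a risk to the quality of the primary safety data, not as a demonstrated loss of events. Followed as written, the schedule asks about non-serious events for the first time 3 weeks after therapy and about 3–5 weeks after the scout dose, although patients are seen at both sessions and at day 3–4. Under-recording and mis-dating of early non-serious events are the likely consequences. Their size cannot be estimated from the documents. The weakness is moderate and cheap to remove.

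The second-lobe matter is a separate ambiguity. With M3 taken as week 13, W6 and M3 fall 0–2 and 7–9 weeks after the second treatment if the clock runs from the first, and there is no gap if it restarts. The finding is that the anchor is undefined, not that follow-up is inadequate.

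**What to change.** 1. Amend the Safety section and Table 1 so that adverse-event and concomitant-medication collection is continuous from the scout dose. Mark it at Scout, at each Treatment session (including a second-lobe session) and at the day 3–4 SPECT.
2. Report ADE onset relative to the most recent exposure.
3. State in Study procedures and Table 1 which treatment starts the week and month count in bilobar patients. The two places must be reconciled, and in agreement with iHEPAR, because the studies are described as identical and will be pooled.

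The first two changes cost a table edit, one or two sentences and a few questions at visits that already take place. The third costs a sentence and a check against iHEPAR. Adding safety visits after a second treatment, or moving the M3 and M6 assessments, is not part of this recommendation. Either would need resources or alter a response schedule shared with iHEPAR, and the documents do not settle whether it is needed.

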### Data collection

Data will be collected using trial-specific patient report forms. As far as possible, missing data will be chased. For the primary analysis, there will be no data imputation for missing data in the primary endpoint. All patient-related data will be held in a secure password-protected electronic database that will only be accessible by the research team.

### Translational endpoints

Using established methodologies,^17^ we will extract radiomic features and correlate these with clinical outcome measures using lasso regression. Images from RHEPaiR will be combined with iHEPAR for analysis. This will allow us to prospectively identify radiologic predictors of outcome to RE.

### Statistical analysis

As this is a pilot study, no formal sample size calculation will be undertaken, and 15 patients will be recruited. Patients enrolled will be combined with the prospective iHEPAR study, which seeks to enrol 30 patients. iHEPAR has an 85% power to detect unacceptable toxicity occurring in 25% of patients. Participants failing screening will not count towards recruitment figures.

A full statistical analysis plan will be drawn up prior to database lock and any data interpretation. No interim analysis is scheduled to occur. The final analysis will be conducted at the end of the study once recruitment and treatment are complete.

The efficacy analysis will consist of the full analysis set (FAS), ie, all patients who received RE. The safety analysis will also be conducted in the FAS. The frequency of ADEs and SADEs will be assessed for severity (NCI-CTCAE v5.0), expectedness, seriousness and causal relationship to treatment. ADEs will be summarised by toxicity, type and timing. An estimation of ORR and its 95% CI will be reported. If appropriate and required, a per-protocol analysis set will be defined/finalised/approved prior to the final analysis on which the primary analysis will be repeated.

Histograms and box plots will be used to check the distribution and possible outliers for continuous variables. Continuous variables that follow a normal distribution will be summarised using means and SD. Skewed continuous variables will be summarised using medians and interquartile ranges. Categorical variables will be summarised using frequencies and percentages.

Any deviation(s) from the final statistical plan in the final analysis will be described and justification given in the final report.

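### The primary device-event incidence is computed only in patients who received RE, so events in patients who had the scout session but no treatment are left out

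*Protocol article*

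**What the plan says.** Trial objectives sets the primary endpoint: "The primary objective is to determine the incidence of adverse and serious adverse device events (ADEs/SADEs) overall and by severity". Statistical analysis fixes the populations: "The efficacy analysis will consist of the full analysis set (FAS), ie, all patients who received RE", followed by "The safety analysis will also be conducted in the FAS". No other safety population is named.

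Study procedures describes what happens before treatment. Patients have a hepatic angiogram. Where aberrant vessels are found, "protective coiling of any extrahepatic branch (eg, aberrant segment IV and right gastric artery) will be undertaken". In the same session a holmium scout dose of at most 250 MBq "will be injected into the hepatic artery via the same catheter position chosen for the scheduled RE session". The plan continues: "Following completion of the angiogram and scout imaging, a decision will be made regarding the dose to be delivered", and "QuiremSpheres (Terumo Europe) will be administered up to 2 weeks following these investigations".

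Table 1 lists the scout dose and the therapeutic dose on separate rows and at separate visits, and marks an eligibility check at Screening, Scout and Treatment. The Safety section counts a serious event as related if it results from the study treatment or from the procedure. On recruitment, Statistical analysis adds: "Participants failing screening will not count towards recruitment figures".

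**The concern.** The intervention under study is RE whose dose is individualised from scout imaging. The scout session is therefore part of the strategy, and it carries risks of its own: arterial catheterisation, possible coiling and injection of a radioactive device. A safety set that begins at therapeutic administration has no place for a patient who was exposed to all of this and then not treated.

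The route out of the set is not neutral. A serious complication at the scout session is a plausible reason not to proceed, so the event that should be counted may be what removes the patient from the count. At stake is whether the primary incidence describes the whole device strategy, as the objective is worded, or only the patients who reached its second step. The results are also to be combined with iHEPAR, and the Discussion expects the combined analysis to yield radiation safety thresholds.

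**Working it through.** The plan has no figure on this point to reproduce. The check is a reading of the text, followed by an illustration.

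**Reading the text**

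1. Does the scout count as RE? The Introduction presents it as work-up, Study procedures places it ahead of a separately scheduled RE session, and Table 1 separates the two doses. A scout-only patient has not received RE.
2. Can a patient be scouted and not treated? The session measures the hepatopulmonary shunt fraction, the dose decision follows it, treatment comes up to 2 weeks later, and eligibility is checked again at the treatment visit. So yes.
3. Is a scout event within the objective? The objective is ADEs/SADEs overall, and relatedness covers the procedure. So yes.
4. Is the event in the primary analysis? Only if the patient goes on to RE.

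**Inputs for the illustration**

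- Treated patients: 15, the planned number (Statistical analysis).
- Scout-only patients k: not in the documents; assumed 1 to 4.
- Probability q that a scout-only patient has an ADE: not in the documents; assumed 5% to 20%.
- Treated patients with an ADE: assumed 3.

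**Effect on the rate**

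With x events among 15 treated patients and s among k scout-only patients, the FAS rate is x/15 and the rate in all exposed patients is (x + s)/(15 + k). The second is the larger when s/k > x/15.

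For x = 3 the FAS rate is 3/15 = 20.0%. With k = 2:

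- s = 0: 3/17 = 17.6%
- s = 1: 4/17 = 23.5%
- s = 2: 5/17 = 29.4%

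The change can therefore go in either direction.

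If no treated patient has an event, 0/15 = 0% (exact 95% CI 0 to 21.8%). One event among two scout-only patients gives 1/17 = 5.9% (0.1 to 28.7%).

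**Share excluded, and chance of losing an event**

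The share of scouted patients outside the safety set is k/(15 + k). The chance that at least one affected patient is omitted is 1 − (1 − q)^k.

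| k | Share outside | q = 5% | q = 10% | q = 20% |
|---|---|---|---|---|
| 1 | 1/16 = 6.2% | 5.0% | 10.0% | 20.0% |
| 2 | 2/17 = 11.8% | 9.8% | 19.0% | 36.0% |
| 3 | 3/18 = 16.7% | 14.3% | 27.1% | 48.8% |
| 4 | 4/19 = 21.1% | 18.5% | 34.4% | 59.0% |

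**The case against.** The strongest defence is that a treated-only set answers a legitimate question. The Discussion says safety must be evaluated because individualised planning departs from the approved 60 Gy average. Only patients given QuiremSpheres have that exposure; the scout activity is capped and, in selective treatments, reduced in proportion to volume. Pooling untreated patients into a single rate could understate therapeutic toxicity. This stands, and it is why the treated FAS should be kept. It does not justify having no other safety set when the objective is worded as ADEs/SADEs overall.

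Secondly, part of the problem is already covered. Scout events in patients who go on to RE stay in the FAS. The Safety section requires all adverse events to be reported and the sponsor to be notified of every SAE. ADEs are to be summarised by timing. This also stands: the loss is from the primary incidence, not necessarily from safety reporting.

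Thirdly, this is a descriptive pilot of 15 patients with no stated toxicity threshold of its own, so no formal decision changes. The two exact intervals above overlap almost entirely. That limits the size of the problem but does not remove it.

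Three stronger readings are tempting and go beyond the documents:

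- A reader might infer that the reported incidence is bound to be too low. Scout-only patients without events would lower the rate, so the direction is not established.
- A reader might infer that a patient harmed at the scout becomes a screen failure and is replaced to reach 15. The text does not say so. The inference rests on a Table 1 heading that appears to place Scout under Screening, in a table whose layout may not have survived extraction.
- A reader might infer that the pooled rate inherits the same exclusion. The article calls iHEPAR identical, but does not show its analysis sets.

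**Conclusion.** The concern holds. As written, the primary safety analysis omits every device event that occurs in a patient who is scouted but not treated, and the omission can depend on the outcome. This follows from a rule the article states, not from detail left to the analysis plan.

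The net effect on the incidence may be up or down, and its size is unknown. The 1 to 4 scout-only patients and ADE rates of 5% to 20% used above are assumptions. Under them, 6% to 21% of scouted patients fall outside the set, and the chance of omitting at least one affected patient runs from 5% to 59%. The illustration also assumes that 15 patients are treated. Whether scout-only patients count towards the 15 is unclear and needs clarifying.

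The treated-only set is not wrong in itself. It is incomplete for the stated objective and should be reported beside an exposure-based set.

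**What to change.** In the protocol, and in the analysis plan before database lock:

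1. Define a safety set of all patients who start the scout session or receive any QuiremScout or QuiremSpheres.
2. Report ADE/SADE incidence by phase: scout-phase events over all scouted patients, therapy-phase events over the RE-treated FAS.
3. Give the overall incidence in all exposed patients, and the number scouted but not treated with reasons.
4. Keep the RE-treated FAS for ORR and for the therapeutic toxicity rate.
5. State whether the Scout visit is part of screening, and whether scouted but untreated patients count towards the 15.

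The cost is a few sentences of text and adverse-event data for a small number of scout-only patients. That collection should be written in explicitly: as extracted, the adverse-event row of Table 1 is marked at Screening and at weeks 3 and 6 and months 3 and 6, with no mark at the Scout visit. The drawback is that scout-only patients without events dilute the overall rate, so it must always be read beside the treated-only rate.
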